**Fig. 1 fig1:**
[figure not shown]
CONSORT diagram for START Together pilot trial.

#### Recruitment

2.2.2

For the current study, women are considered the “index participant” meaning that they are initially identified as potentially eligible and recruited for study participation. Women with HIV who are non-adherent to their ART are recruited from local clinics. Specifically, clinic registries identify community members who have missed their monthly clinic appointments to pick up their ART and/or who are virally unsuppressed. Potentially eligible women, from these lists or who are otherwise attending these participating clinics, are informed about the study. Women provide verbal consent to complete the screening procedures. Screening takes place over the phone or in-person in private rooms. The screening assesses preliminary eligibility for the study including demographic factors (age, relationship status, etc.) and self-reported difficulties with ART adherence. To assess relationship status, we ask women whether they are in a “committed romantic relationship.”

Women who meet the preliminary eligibility criteria via the screener are asked about their partner's desire to be involved. Contact information for the study is provided to the male partner via the female participant. The male partner then contacts study staff to undergo screening procedures to assess preliminary eligibility. Once male partners complete screening and meet preliminary eligibility, the couple undergoes the consent process together. Potential participants are informed that they cannot be deemed eligible to participate until their partners are screened and both members of the couple complete the baseline assessment.

Informed consent is completed by trained staff members. Additional consent is obtained to extract data from participants' medical charts. Once consented, each member of the couple completes their baseline assessment separately. Assessments are conducted by research assistants of the same gender as the participants, if possible. During the baseline assessment, the assessor asks participants about their willingness to participate in the study as an additional strategy to ensure participants are not being coerced into study participation. Furthermore, the baseline assessment is used to further verify that the couple is in a bona fide romantic relationship given our team's past experiences recruiting couples where non-couples have feigned being a relationship in order to enroll in the study [22]. To ascertain the couple is in a bona fide romantic relationship, we ask a few informational questions to each participant regarding the partner; responses are compared after the assessment is complete. Examples of these questions include location/area of where the partner was born, employment status, and educational attainment. Similar procedures have been used in the recruitment of couples for intervention studies at this location [10].

The baseline assessment includes a battery of measures that assess previous HIV infection and treatment history, domains pertinent to relationship functioning (e.g., trust, intimacy, sexual satisfaction), and healthcare utilization. All measures have undergone a translation and back-translation process from English into isiZulu. All women (and any men who report being HIV-positive) complete a dried blood spot test to determine viral load (one of the possible ART non-adherence eligibility criteria for women) if a recent (past 30 days) viral load test is unavailable in their medical records.

Couples who meet all eligibility and none of the exclusion criteria above are eligible for study participation and randomized to either TAU or START Together by study staff initiating the randomization function in REDCap. Post-randomization, couples complete the study interventions and assessments according to those in Table 1. For START Together couples, they must initiate the first treatment session within 12 weeks of randomization. We did not a priori set an upper limit on the length of time couples were required to complete the intervention sessions by, to allow for flexibility in this pilot study.

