**Methods:**

Women (*N* = 20) who were not engaged with ART adherence (defined via self-reported ART difficulties, record of missed clinic visits, or viral non-suppression) are the target patients; male partners are not required to know or disclose their HIV status to be part of the study. Couples are randomized 1:1 to the experimental treatment (START Together) or treatment as usual (referrals to the local clinic to support ART adherence or any other HIV-related care). START Together is a 5-session intervention based in cognitive-behavioral couple therapy, which is a skill-based intervention focusing on communication and problem-solving skills, and Life Steps, a problem-solving intervention identifying barriers and solutions to medication adherence. Couples are assessed at baseline, post-treatment (8 weeks post-randomization), and follow-up (12 weeks post-randomization).

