**Table 1 tbl1:**
[figure not shown]
Schedule of study enrollment, intervention, and assessments.

Follow-up assessments are scheduled 8- and 12-weeks post-randomization. Each participant in the couple receives ZAR 120 cash (∼$8.50 USD) for each completed research assessment as reimbursement for their time and effort. They do not receive an incentive for attending the intervention. If couples do not complete the treatment as intended, they are still eligible to complete the research assessments. Study assessors are not blinded to couples’ treatment condition due to practical constraints of a small research team.

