#### START Together

2.3.2

The 5-session intervention is based on the principles of cognitive-behavioral couple therapy (CBCT) applied to HIV treatment [7] and Life Steps for ART adherence [23]. CBCT is behavioral therapy approach focused on skills training in order for couples to improve communication and problem-solving skills, with the ultimate goal of improved relationship functioning [24]. The principles of CBCT (i.e., working with dyads, skills training related to communication and problem-solving) have been applied to the treatment of numerous medical problems including hypertension, diabetes, and chronic obstructive pulmonary disease [25]. Uthando Lwethu, a CBI with South African couples to promote couples HIV counseling and testing, used communication and problem-solving skills as central components and showed significant improvements in rates of couples testing for HIV together [10].

Formative work for the current intervention revealed the acceptability of learning and using couple-level communication and problem-solving skills in a therapeutic setting (i.e., with a counselor) by both women and men [26]. Furthermore, the intervention incorporates Life Steps, a one-session intervention based on the principles of problem-solving therapy [23]. It focuses on identifying barriers to ART adherence as well as feasible solutions in the form of devising plans and back-up plans. Life Steps has been adapted for the South African context [27] and has previously been used to promote ART adherence in individuals with depression [28] and substance use [29] in South Africa. Life Steps has previously been adapted for delivery to dyads as an optional session for PrEP adherence in Uganda [30] and in the US for serodiscordant male couples [31].

For the current study, the intervention has 5 sessions of fixed content. However, couples can complete up to 3 additional booster sessions (i.e., 8 sessions total), depending on the couple's preference or need for additional support. This is decidedly jointly with the intervention provider (i.e., interventionist). Couples who enroll in treatment for more sessions spend more time addressing barriers to ART adherence or other HIV or relationship issues. Both partners must be present for a session to be carried out—couples are made aware of this during the informed consent process. Intervention sessions take between 60 and 75 min. Table 2 presents an overview of the content for the 5-session intervention.

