#### Implementation outcomes

2.5.1

***Feasibility.*** Defined as the suitability, fit, or utility of the intervention in the current setting [35]. This is measured using (1) the percentage of couples assigned to START Together who agree to enroll in the intervention and (2) a 14-item feasibility subscale of a validated implementation science measure designed for pragmatic mental health interventions in global low-resource settings [36]. Only couples randomized to START Together complete the feasibility measure and patients and partners complete the form separately at 8-weeks.

***Acceptability.*** Defined as the tolerability or satisfaction of the intervention [35]. This is measured by (1) assessing couple's attendance and retention in the intervention and (2) a 15-item acceptability subscale of the validated implementation science measure designed for global low-resource settings [36]. Only couples randomized to START Together complete the acceptability measure and patients and partners complete the form separately at 8-weeks.

***Fidelity.*** A randomly selected subset (20%) of the intervention sessions are translated from isiZulu to English and rated for fidelity by an independent rater who is trained in the protocol. The rater assesses content fidelity specific to the intervention, adapted from fidelity for a CBCT for depression intervention in a high-resource setting [37], as well as process fidelity (e.g., verbal communication, being non-judgmental) adapted from prior research on common therapist factors in low-resource settings [38].

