### Power, sample size, and data analysis

3.1

The primary efficacy outcome, for which a power analysis can be calculated, is women's viral suppression. Only one prior study examined the efficacy of a CBI for ART adherence with serodiscordant couples in the US and found that after a 4-session intervention, 47% of the intervention group compared to 25% of the control group (who received referrals to medical provider) had at least 90% adherence to their ART [45]. Based on this, a power analysis was conducted using G*Power 7 [46] comparing the proportion of the sample reaching viral suppression between the two treatment arms.^2^ Using a two-tailed test and equal allocation of the sample between the two treatment arms, to achieve a power of .80 would require a total *N* = 148 (*n* = 74 in each arm). Because the current study is a pilot trial focused on feasibility and acceptability of the proposed intervention and collecting preliminary efficacy data on the intervention, our sample size will be *N* = 20 couples (*n* = 10 couples in each arm). A sample size of 20 represents the smallest sample size deemed appropriate for any statistical modeling [47]. The study will therefore be underpowered to detect significant differences between study arms in the efficacy outcome. We will instead focus on the direction of effects.

Descriptive statistics will be reported for implementation outcomes. For feasibility and acceptability, the proportion of the sample meeting the definitions used to define these constructs (see Measures) will be reported. Means, standard deviations, and ranges will be reported for the self-report measures of feasibility and acceptability, as well as for fidelity. We will compare these descriptives to previous behavioral couple- and family-based interventions in sub-Saharan Africa [10,48].

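### The feasibility and acceptability questionnaires are fixed at week 8, but the first session may fall as late as week 12, so some couples may rate a course they have not begun or not finished

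*Protocol article*

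**What the plan says.** All references are to the protocol article.

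- **Start of treatment (2.2.2 Recruitment).** The rule for the intervention arm reads: "they must initiate the first treatment session within 12 weeks of randomization. We did not a priori set an upper limit". The limit left unset is the time allowed for completing the sessions. The reason given for leaving completion open is flexibility in a pilot.
- **Timing of the forms (2.5.1 Implementation outcomes).** For feasibility: "Only couples randomized to START Together complete the feasibility measure and patients and partners complete the form separately at 8-weeks". For acceptability: "Only couples randomized to START Together complete the acceptability measure and patients and partners complete the form separately at 8-weeks". The condition is the arm assigned, not whether a session has taken place.
- **What acceptability means (2.5.1).** "Defined as the tolerability or satisfaction of the intervention".
- **The week-8 visit (Abstract, Methods).** "Couples are assessed at baseline, post-treatment (8 weeks post-randomization), and follow-up (12 weeks post-randomization"). The clock starts at randomization, and week 8 carries the post-treatment label.
- **Couples who do not finish (text after Table 1).** "If couples do not complete the treatment as intended, they are still eligible to complete the research assessments".
- **Reporting (3.1).** "Means, standard deviations, and ranges will be reported for the self-report measures of feasibility and acceptability, as well as for fidelity".

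**The concern.** The window for a first session runs four weeks beyond the only time the two questionnaires are given. A couple can obey both timing rules and still be due to rate its satisfaction with something it has not received. Other couples may be partway through. Nothing in the article delays the forms for late starters or links a rating to the sessions received when it was given.

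Late starts are plausible because "Both partners must be present for a session to be carried out", so one unavailable partner postpones a session. The Discussion itself lists treatment attendance among the expected challenges.

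Feasibility and acceptability belong to the trial's first objective, and section 3.1 concedes that the efficacy comparison is underpowered. The questionnaire scores are thus among the main products of the pilot, and section 3.1 plans to set the implementation results beside those of earlier couple- and family-based interventions. A mean that mixes ratings of a complete, a partial and an unreceived course would be hard to interpret.

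**Working it through.** **Inputs from the article.** Forms at week 8 from randomization (2.5.1; Abstract). First session at any time in weeks 0 to 12, with no completion limit (2.2.2). Five fixed sessions; the optional boosters are ignored here (2.3.2). Ten couples per arm (3.1), two partners each, with separate forms (2.5.1). The article gives no figure of its own on this point to reproduce.

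**Assumption.** The article gives no session spacing, so gaps of one and two weeks are both shown.

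**Step 1: sessions received at a visit.** For start week s, gap g and visit week v, the number held is min(5, floor((v − s)/g) + 1) if s ≤ v, and 0 otherwise.

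| Start week | Week 8, weekly | Week 8, fortnightly | Week 12, weekly | Week 12, fortnightly |
|---|---|---|---|---|
| 0 | 5 | 5 | 5 | 5 |
| 2 | 5 | 4 | 5 | 5 |
| 4 | 5 | 3 | 5 | 5 |
| 5 | 4 | 2 | 5 | 4 |
| 6 | 3 | 2 | 5 | 4 |
| 8 | 1 | 1 | 5 | 3 |
| 10 | 0 | 0 | 3 | 2 |
| 12 | 0 | 0 | 1 | 1 |

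- A start in weeks 9 to 12 gives 0 sessions at week 8 at any pace. This result needs no assumption about spacing.
- At a weekly pace, all five sessions are held by week 8 only for starts up to week 4 (4 + 4 = 8).
- At a fortnightly pace, that holds only for a start at week 0 (0 + 8 = 8).
- At week 12, every permitted start has at least one session, provided a week-12 session precedes the form.

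The rows are permitted start weeks, not couples. They say nothing about how often each occurs.

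**Step 2: weight of one couple.** If all forms are returned there are 10 × 2 = 20. One couple contributes 2/20 = 10% of the mean.

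**Step 3: illustrative shift.** Let m couples be affected, and let d be the gap between their early rating and the one they would give later. The mean moves by (m/10) × d. Take d = 0.5 to 1 SD (assumed):

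- m = 1: 0.05 to 0.10 SD
- m = 3: 0.15 to 0.30 SD

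**Step 4: yardstick.** With partner correlation r, the standard error of the mean is SD × √((1 + r)/20). For r = 0.3 it is √(1.3/20) = 0.255 SD; for r = 0.5 it is √(1.5/20) = 0.274 SD (both r assumed). Three couples with d = 1 SD therefore shift the mean by 0.30/0.274 = 1.10 to 0.30/0.255 = 1.18 standard errors. One couple with the same gap shifts it by 0.10/0.274 = 0.36 to 0.10/0.255 = 0.39.

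**The case against.** The best defence is that the schedule in Table 1 is not shown and that week 12 looks like an outer limit, not the plan. The post-treatment label on week 8 suggests that most couples were meant to be finished by then. This limits what can be said about frequency. It does not remove the mismatch, because the week-12 allowance and the week-8 forms are both stated outright, and section 2.5.2 does list week 12 where a measure is repeated. The flexibility argument covers the open completion date, not the single form date.

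A second defence is that attendance and retention are reported as part of acceptability, so readers will see uptake beside the ratings. That stands in part. They would not necessarily see how many sessions lay behind each rating.

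Four stronger readings are tempting and are not supported:

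- **Partial-course ratings are invalid.** They are not. A couple can judge satisfaction after some sessions, and a couple struggling to start may have a relevant view of feasibility. The clear problem is the acceptability form completed before any session.
- **Many couples will be affected.** The start distribution is unknown. The 83% full attendance cited in the Discussion comes from a different, four-session intervention and concerns non-completion. Couples who drop out would be unfinished whenever the form was given, so that figure does not measure this problem.
- **The efficacy comparison is compromised.** A late start can put the week-12 visit before the end of treatment, but comparing couples as randomized remains valid. Any effect on the size of the difference has not been computed.
- **A go/no-go decision is at risk.** The article states no threshold for these scores.

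**Conclusion.** The point holds as a mismatch between two stated timing rules. That a couple starting in weeks 9 to 12 is due to complete the acceptability form before any session follows from the text alone. That couples starting after week 4 rate an unfinished course rests on an assumed weekly pace; slower sessions would bring in earlier starters too.

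The practical effect is uncertain. One affected couple is minor. On the assumed score gaps and correlations, it takes about three couples and the largest gap for the shift to exceed one standard error, and nothing in the article says that three would start late. The harm is confined to how the two questionnaire summaries are read. This is a cheap improvement to first-objective data, not a flaw in the trial's validity.

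**What to change.** 1. Keep the week-8 and week-12 visits fixed from randomization in both arms.
2. Repeat the two questionnaires at the existing week-12 visit for couples who had not finished the five fixed sessions by week 8.
3. Record the number of sessions received when each form is completed, and label partial-course ratings as such.
4. Use in the summary mean the latest rating given after at least one session.
5. Count couples with no session as non-uptake and do not pool their satisfaction scores.

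A week-4 target for the first session is optional. At a weekly pace it brings session 5 to week 8; at a fortnightly pace only three sessions are held by then, so it does not replace the repeat. It must not exclude couples who start later.

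The cost is brief protocol wording and one conditional REDCap form at a visit that already exists. The drawbacks are that form timing will differ between couples (week 8 or week 12), and that late starters may still be mid-course at the repeat: at a weekly pace, starts in weeks 9, 10, 11 and 12 have 4, 3, 2 and 1 sessions by week 12. Item 3 makes that visible.

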**Table 1 tbl1:**
[figure not shown]
Schedule of study enrollment, intervention, and assessments.

Follow-up assessments are scheduled 8- and 12-weeks post-randomization. Each participant in the couple receives ZAR 120 cash (∼$8.50 USD) for each completed research assessment as reimbursement for their time and effort. They do not receive an incentive for attending the intervention. If couples do not complete the treatment as intended, they are still eligible to complete the research assessments. Study assessors are not blinded to couples’ treatment condition due to practical constraints of a small research team.

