#### Efficacy outcomes

2.5.2

***Women's ART adherence.*** The amount of HIV viral copies extracted from medical records (past 30 days) or dried blood spots is used as an indicator of adherence to ART. A viral load of <50 c/mL is considered virally suppressed according to South African guidelines [19]. This is supplemented with participants' self-report of adherence to ART using the 3-item Ira Wilson adherence measure [39], which has been previously used in South Africa [40,41]. Blood samples are stored in a secure area at the Human Sciences Research Council and are tested by a local laboratory service. Viral load is collected at baseline and 12-weeks and self-report ART adherence is collected at baseline, 8-weeks, and 12-weeks.

***Men's engagement in HIV care.*** Dichotomous engagement in care (yes/no) is extracted from men's clinical records (if available) and supplemented with self-report at 12-weeks. Appropriate engagement in care depends on men's HIV status and current level of engagement. For men who are HIV-negative, receiving an HIV-test after 3 months is appropriate engagement in care. For men who are living with HIV but are not taking ART, initiating ART is the next appropriate step in the HIV care cascade. For men living with HIV who take ART but are not virally suppressed, improving adherence and achieving viral suppression is the next level of care engagement. Regardless of men's initial level of care engagement, achieving the next milestone in the HIV care cascade is recorded as positive for engagement in care.

***Couple's relationship functioning.*** A 39-item self-report measure assessing factors of relationship functioning was developed based on qualitative work assessing local definitions of healthy relationships with men and women in committed relationships from Cape Town and Vulindlela communities [42,43]. The factors are active relationship building, open communication, and couple-level problem-solving.^1^ Preliminary quantitative data from this measure show adequate reliability of the constructs, with alpha values ranging from .69 to .81 [44]. Assessment occurs at baseline, 8-weeks, and 12-weeks.

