### Conclusion

4.1

Overall, this study provides the first empirical test of an intervention that seeks to simultaneously address the differing needs of men and women throughout the HIV care cascade. Study strengths include testing a theoretically driven intervention, using a standard of care control group, using objective measurement (i.e., viral load, medical chart information) where possible, and collecting both implementation and preliminary efficacy outcomes. Primary study limitation is the use of a small sample size, though appropriate for a pilot study, will limit conclusions about strength of any observed effects. Nevertheless, the results of the study will provide an initial empirical basis as to whether the proposed approach provides a promising avenue for future research.

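### Men's engagement in care rests partly on self-report, under man-specific milestones, in a trial with unblinded assessors. No confirmed version is set beside it, although efficacy will be read by direction with 10 couples per arm.

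*Protocol article*

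**What the plan says.** All references are to the protocol article.

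- **Blinding (section 2.2.2, text under Table 1).** "Study assessors are not blinded to couples’ treatment condition due to practical constraints of a small research team".
- **Source of the men's outcome (section 2.5.2).** "Dichotomous engagement in care (yes/no) is extracted from men's clinical records (if available) and supplemented with self-report at 12-weeks".
- **Man-specific target (section 2.5.2).** "Appropriate engagement in care depends on men's HIV status and current level of engagement". Three stages are listed: HIV-negative men are to be tested again, men with HIV who are not on ART are to start it, and the third is set out as follows: "For men living with HIV who take ART but are not virally suppressed, improving adherence and achieving viral suppression is the next level of care".
- **Scoring rule (section 2.5.2).** "Regardless of men's initial level of care engagement, achieving the next milestone in the HIV care cascade is recorded as positive for engagement in care".
- **Men's viral load at baseline (section 2.2.2).** "All women (and any men who report being HIV-positive) complete a dried blood spot test to determine viral load", unless the medical records hold a result from the past 30 days. A 12-week viral load is mentioned only in the paragraph on women's adherence. Table 1, the assessment schedule, is not shown.
- **Reading of efficacy (section 3.1).** Women's viral suppression is the primary efficacy outcome. The trial is acknowledged to be underpowered, with 10 couples per arm, and attention will go to the direction of effects.
- **Stated strength (section 4.1).** "using objective measurement (i.e., viral load, medical chart information) where possible".

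**The concern.** The men's outcome takes three steps: place the man on the care cascade, identify the milestone that counts for him, and decide whether he reached it. Where no clinical record is available, the last step falls back on what he says. Men in START Together are offered five sessions on HIV and adherence with their partner; men in TAU are given referrals. Each man knows his arm, and so does the person assessing him. Over-reporting by men who had the sessions, or more generous reading of their answers, would favour START Together.

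In a powered trial a small shift of this kind would be set against a confidence interval. Here the stated reading is the direction of effect, so the sign of the difference carries the message. With 10 men per arm, one man is 10 percentage points. The article discusses how varied the men's outcome is (section 4) but does not discuss how unblinded assessment may act on it, and it does not separate results confirmed by a record from results that rest on report alone.

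**Working it through.** **1. The plan's own figure.** Section 3.1 gives a total of 148 for 80% power, two-tailed, equal allocation, 47% v 25%. With alpha 0.05 (assumed; the article does not state it) and pooled variance:

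n per arm = [z(0.975)·√(2·p̄(1−p̄)) + z(0.80)·√(p₁(1−p₁) + p₂(1−p₂))]² / (p₁−p₂)², where p₁ = 0.47, p₂ = 0.25, p̄ = 0.36.

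This gives 74 per arm, 148 in total, with power 0.803. The stated figure reproduces. With 10 per arm the same comparison has power of about 0.17, in line with the article's own statement that the trial is underpowered. The point here does not depend on this figure; it shows why direction is all that is left to read.

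**2. Sensitivity of the direction to a small shift.** Inputs:
- 10 men per arm, all with an outcome (section 3.1; no missing values assumed).
- True engagement rate p, the same in both arms (assumed; the article gives none). Main value 40%, range 25% to 50%.
- Net shift d in START Together only, from over-reporting or lenient scoring (assumed; the article gives none). Values 0, 5, 10 and 15 points.

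With A ~ Binomial(10, p+d) for START Together and B ~ Binomial(10, p) for TAU, independent:

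P(START Together strictly ahead) = Σₐ P(A=a)·P(B<a), a = 0 to 10.

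| d | p = 25% | p = 40% | p = 50% |
|---|---|---|---|
| 0 | 0.397 | 0.410 | 0.412 |
| 5 points | 0.501 | 0.501 | 0.502 |
| 10 points | 0.599 | 0.592 | 0.592 |
| 15 points | 0.688 | 0.677 | 0.679 |

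At p = 40% the chance that TAU is strictly ahead falls from 0.410 (d = 0) to 0.325 (5 points) and 0.248 (10 points); the remainder is ties. The assumed true rate hardly matters over this range. The size of the shift does.

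**3. What protects the outcome, and what does not.**
- Clinical records come first, and study assessors do not create them. If, for example, half of the men had a usable record, a 10-point shift confined to the other half would be a net 5 points (0.5 × 10), the second row of the table.
- For the three listed stages the milestone follows from HIV status, treatment history and viral load, which the baseline assessment collects before randomization. The text does not say that the milestone is written down at that point. It lists no milestone for a man who is already suppressed, and men need not know or disclose their status to take part, so not every man's target can be read off the listed rules.
- No rule is stated for a record and a self-report that disagree.

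**The case against.** The case on the other side is substantial, and much of it stands.

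- **Disclosure and rank.** Lack of blinding is stated openly with a reason, and men's engagement is not the primary efficacy outcome. Section 4 already urges care with the men's data. This limits the weight of the point but does not address the self-reported component.
- **Objective sources.** A reader might infer that the outcome has no protected component at all. That is not supported: clinical records are the first-named source, and a viral load is a laboratory result.
- **Who scores.** A reader might infer that the unblinded assessors themselves judge the milestone. The text does not say who does.
- **Self-reported suppression.** A reader might infer that viral suppression in men is taken from their own word. The article never says so. The sentence on self-report is general, men who report being HIV-positive have a baseline blood spot if no recent result is on file, and Table 1, which is not shown, may schedule a 12-week sample for men.
- **Objectivity claim.** A reader might see a contradiction with the strength claimed in section 4.1. There is none: that claim is limited to where such measurement is possible, which agrees with records being used if available.
- **Size and direction of bias.** Both are assumed. The mechanism is plausible, but the documents give no misclassification rate.
- **Masked scoring.** It would not remove bias from men who know their own arm, and a small team may have nobody free to do it. This stands, so it is only optional below.

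**Conclusion.** The point holds in a limited form. Men's engagement is a man-specific yes/no outcome, partly self-reported, in a trial whose assessors know the arm, and it will be read by direction with 10 couples per arm. The self-reported part is open to arm-related reporting or scoring, and the visible text sets no confirmed version beside it.

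On the illustration above, a net shift of 5 points in START Together alone takes the chance that it looks better from 41% to 50%, and a shift of 10 points takes it to 59%, with no true difference. These figures rest on an assumed common true rate (40%; 25% to 50% gives nearly the same), complete data on 10 men per arm, and a shift in one arm only. They show how sensitive the reading is and do not forecast the bias. The documents do not establish that such a bias will occur, that assessors score the milestone, or that suppression is self-reported. The change is worth making because it costs little and the outcome is one of the three that the trial sets out to examine.

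**What to change.** 1. Derive each man's cascade stage and the one milestone that will count for him from baseline data, and lock both in REDCap before the randomize button is clicked. State how a man who is already suppressed, or whose status is unknown, is to be scored.
2. Count the viral-suppression milestone as reached only on a laboratory or clinical-record value. If Table 1 or the full protocol already schedules a 12-week viral load for men, say so in section 2.5.2.
3. Report engagement confirmed by record or laboratory, by arm, alongside the version supplemented with self-report. Give the number of men in each arm whose outcome rests on self-report alone. Call a direction of effect supported only if both versions agree.
4. Optional, if an existing team member is available: have the 12-week milestone scored from a de-identified extract with the arm removed.

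**Cost.** One locked REDCap form, one sentence in the outcome definition, and one extra table for about 20 men. **Downsides.** The confirmed version will have more missing values, record availability may itself differ by arm, and the men's own reporting bias remains in the supplemented version. For these reasons the two versions are best shown together, without making the confirmed one the lead.
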